#### **\*\*4.1.2 Severity\*\***

- Mild: Discomfort is usually transient, not interfering with daily life and normal activities.

#### **\*\*4.2 Adverse Event Handling, Follow-up, and Serious Adverse Event Reporting\*\***

> The investigator shall explain in detail to the subject, requiring the subject to truthfully report any changes in condition after receiving the intervention treatment. Physicians should avoid leading questions. While observing efficacy, close attention should be paid to adverse events, analyzing causes and making judgments. For any AE occurring during the study, details such as time of onset, symptoms, duration, measures taken, and outcome should be recorded in the medical record/Case Report Form, and its relationship to the investigational intervention should be assessed; for those with abnormal laboratory findings, follow up until results return to normal or to pre-treatment levels. In case of an SAE, a Serious Adverse Event Form should be completed and reported to the Hospital Medical Ethics Committee and the IIT Project Management Office within 24 hours.

#### **\*\*4.3 Assessment of Adverse Event Relatedness\*\***

> The investigator shall assess the potential relationship between the adverse event and the investigational intervention. The criteria for judging the relationship are as follows:

> ① Definitely not related: The AE has no reasonable possibility of being caused by the investigational intervention.

> ② Probably not related: Evidence suggests the event is more likely related to other factors (e.g., concomitant medication, concurrent illness), but a relationship to the intervention cannot be ruled out.

> ③ Possibly related: The event occurs in a reasonable time sequence following intervention administration, and could possibly be caused by the intervention. Cannot be ruled out if possibly caused by other factors (e.g., concomitant medication, concurrent illness). Withdrawal/rechallenge information unavailable or unclear.

> ④ Definitely related: The event type is a known reaction of the intervention, and cannot be explained by other reasons (e.g., concomitant medication, concurrent illness). The temporal relationship strongly suggests causality (e.g., response to withdrawal/rechallenge).

> ⑤ Not assessable: Insufficient information to make a judgment regarding causality. The investigator may change the causality assessment based on subsequent follow-up information and modify the corresponding AE/SAE report.

### **\*\*5. Data Collection and Management\*\***

#### **\*\*5.1 Data Collection\*\***

> Electronic data recording.

## **\*\*5.2 Data Management\*\***

Use EXCEL for data entry, organization, and database establishment.

## **\*\*6. Statistical Analysis Plan\*\***

### **\*\*6.1 Sample Size Estimation\*\***

Sample size was determined using  $N = 2 \cdot [(Z_{\alpha/2} + Z_{\beta})\sigma/d]^2$  and statistical power analysis software G\*Power 3.1. Referring to the effect size observed in studies like Dawson et al. (Cohen's  $d=0.632$ ), with  $\alpha=0.05$  and statistical power  $(1-\beta)$  equal to 80%, the estimated sample size per group should be 34. Considering a 10% clinical dropout rate, the sample size per group was adjusted to 38, totaling 114 participants across three groups.

\*Reference: Dawson J, et al. Vagus nerve stimulation paired with rehabilitation for upper limb motor function after ischaemic stroke (VNS-REHAB): a randomised, blinded, pivotal, device trial. Lancet. (2021) 397:1545–53.\*

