**\*\*Figure 1 Schematic Diagram of taVNS Treatment Operation and Mechanism\*\***

**\*\*(3) Current Status and Shortcomings of taVNS in Reconstructing Stroke Motor Function\*\***

Numerous basic animal experiments and clinical trials have shown that taVNS can promote motor reconstruction after stroke and improve motor function. In 2021, Dawson et al. published a series of studies in *Lancet* and *Neurorehabilitation and Neural Repair*, using randomized double-blind clinical trials, demonstrating that implanted VNS combined with motor function training was significantly more effective than sham VNS combined with motor function training for upper limb motor function rehabilitation in ischemic stroke patients. Since then, extensive attention has been paid to the effect of non-invasive taVNS on the recovery of motor dysfunction after stroke. Bashar et al. used a clinical trial to show that closed-loop taVNS (Motor Activated Auricular Vagus Nerve Stimulation, MAAVN) could improve the upper limb Fugl-Meyer motor function score and quality of life in stroke patients. The current mechanisms of taVNS for treating post-stroke motor dysfunction mainly include: reducing neuronal apoptosis in the stroke area, reducing infarct volume, regulating neurotransmitter release, inhibiting the activation of neuroinflammatory factor-related pathways, enhancing neural circuit plasticity, and altering blood-brain barrier permeability.

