#### **\*\*3.3 Study Groups and Interventions\*\***

To verify the clinical efficacy and safety of bilateral taVNS for stroke motor dysfunction, and its difference compared to unilateral left-sided taVNS, this clinical trial is divided into three groups:

- (1) **\*\*Conventional Treatment Group:\*\*** Based on drug therapy, provide conventional rehabilitation treatment for stroke hemiplegic motor dysfunction, including comprehensive rehabilitation such as exercise therapy, occupational therapy, physical agent therapy, conventional acupuncture, etc.
- (2) **\*\*Left-sided taVNS Group:\*\*** Based on the conventional treatment group, provide classic non-invasive left-sided auricular vagus nerve electrical stimulation. taVNS parameters: left ear, frequency 25Hz, pulse width 300us, current 6 mA.
- (3) **\*\*Bilateral taVNS Group:\*\*** Based on the conventional treatment group, provide non-invasive bilateral auricular vagus nerve electrical stimulation. taVNS parameters: both ears, frequency 25Hz, pulse width 300us, current 6 mA.

**\*\*taVNS Treatment Regimen:\*\*** 30min/session, 2 sessions/day, 6 days/week, for 4 weeks.

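### The 34 per group in Section 6.1 does not follow from the printed formula, which gives 40 (41 by t-test); at 34 evaluable per arm the stated inputs give about 73% power, not 80%

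*Protocol*

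**What the plan says.** Section 6.1 gives the per-group size as twice the square of (Z at alpha/2 plus Z at beta) times sigma over d. It also cites "statistical power analysis software G\*Power 3.1", without naming the test run in it. The inputs are a Cohen's d of 0.632 from a published trial, alpha 0.05 and 80% power, and the result is that "the estimated sample size per group should be 34". The section continues: "Considering a 10% clinical dropout rate, the sample size per group was adjusted to 38, totaling 114 participants across three groups". The synopsis entry on planned sample size carries the same formula, inputs and results.

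Section 1(3) describes the evidence from the group whose trial supplies d: "implanted VNS combined with motor function training was significantly more effective than sham VNS combined with motor function training", for the upper limb in ischaemic stroke. Section 3.3 explains the three arms partly by the wish to study bilateral taVNS "its difference compared to unilateral left-sided taVNS". Section 6.1 does not say which pairwise contrast its calculation covers, and gives no separate effect size for bilateral versus left.

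**The concern.** The formula, its inputs and its result all stand in the same short section, so the result can be checked directly, and it does not come out. The shortfall of 6 or 7 per arm is too large to be rounding, and it carries through the dropout step into the total of 114. The trial would therefore be approved, run and reported with a power claim that its own calculation does not support. Because neither the contrast nor the test is named, a reader also cannot tell whether the 80% is meant for bilateral versus conventional, left versus conventional, bilateral versus left, or an overall three-group test.

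**Working it through.** **Inputs (Section 6.1 and synopsis).** d = 0.632, standardised, so sigma = 1; alpha = 0.05, two-sided because the formula uses Z at alpha/2; power 80%; dropout 10%; three equal groups.

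**1. The plan's own formula.** n = 2 × (1.960 + 0.842)² / 0.632² = 39.3, so 40 per group. The plan states 34.

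**2. Exact two-sided two-sample t-test (noncentral t).** n = 40 gives 79.7% and n = 41 gives 80.7%, so 41 per group.

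**3. Dropout step.** 34 / 0.9 = 37.8, so 38, and 3 × 38 = 114. This step reproduces, so the error lies in the 34.

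**4. Power at the planned size, one unadjusted pairwise contrast, d = 0.632.**

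| Evaluable per arm | Printed formula (z) | Two-sided t-test |
|---|---|---|
| 34 | 74.1% | 72.8% |
| 38 (no dropout) | 78.7% | 77.6% |
| 40 | 80.7% | 79.7% |
| 41 | 81.6% | 80.7% |

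The d detectable with 80% power at 34 per arm is 0.68 by the formula and 0.69 by the t-test.

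**5. Can another route give 34?**
- One-sided alpha 0.05: 31 by the formula, 32 by t-test. Neither is 34, and both contradict Z at alpha/2.
- One-sided Mann-Whitney test: 32 / (3/π) = 33.5, so 34.
- Three-group one-way ANOVA with f = d/2 = 0.316: 34 per group (power 81.0%).

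The last two give 34, but the protocol states neither. The conversion f = d/2 holds for two groups. With three equal groups whose extreme means differ by 0.632, f runs from 0.632 × √(1/6) = 0.258 (third mean midway) to 0.632 × √2/3 = 0.298 (third mean equal to one extreme). That needs 50 to 38 evaluable per group.

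**6. Baseline adjustment.** With a baseline correlation r, the formula's n is multiplied by (1 − r²): 39.3 × 0.91 = 35.8 at r = 0.3; 39.3 × 0.84 = 33.0 at r = 0.4; 39.3 × 0.75 = 29.5 at r = 0.5. The break-even for 34 is r = √(1 − 34/39.3) = 0.37. This applies only if d is scaled to the raw-score SD, which the protocol does not say.

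**7. Bilateral versus left, 34 per arm, two-sided t-test.** At the plan's d = 0.632, power is 73%. For smaller differences, which are assumptions and not figures from the protocol:

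| Assumed d | 0.2 | 0.3 | 0.4 | 0.5 |
|---|---|---|---|---|
| Power | 13% | 23% | 37% | 53% |

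**8. Size that matches the stated inputs.** Formula: 40 / 0.9 = 44.4, so 45 per arm, 135 in total. T-test: 41 / 0.9 = 45.6, so 46 per arm, 138 in total.

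**The case against.** The best defence is that the 73% describes an unadjusted t-test at one time point, whereas Section 6.2 plans a linear mixed model on repeated measurements. If that model uses the baseline score, if the baseline correlation is about 0.4 and if d refers to the raw-score SD, 34 evaluable per arm would give 80%. This stands as a possibility, and it rules out saying flatly that the trial cannot have 80% power. It does not rescue Section 6.1, which prints an unadjusted formula and assumes no correlation.

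A second defence is that 34 came from a different G\*Power routine. That may well be so, since two routes return 34. But neither is stated, the one-sided route contradicts the printed formula, and the ANOVA route rests on a conversion that fails for three groups.

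Three stronger readings are tempting and are not supported:
- A reader might infer that power for bilateral versus left is far below 73%. The documents give no effect for that contrast, so the low figures rest wholly on assumed smaller differences.
- A reader might compute a joint power for FMA-UE and FMA-LE. Section 3.8.1 lists both as primary but sets no rule that both must succeed.
- A reader might say that the trial will present a null bilateral-versus-left result as equivalence. The protocol makes no equivalence claim.

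Whether an effect from implanted VNS versus sham in the upper limb after ischaemic stroke carries over to non-invasive taVNS, to FMA-LE and to haemorrhagic stroke is a judgement about an assumption, separate from the arithmetic.

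**Conclusion.** Wrong as written, in both Section 6.1 and the synopsis. The stated formula and inputs give 40 per group, or 41 by t-test, against the stated 34: a shortfall of 6 or 7 evaluable patients per arm. On the same inputs, the planned size supports about 73% power rather than 80%, for one two-sided, unadjusted pairwise contrast on one FMA endpoint, with 10% dropout. Full retention of 38 per arm would still leave the t-test at 77.6%. Where the 34 came from is conjecture, and the finding does not depend on it. For bilateral versus left, the supportable statement is that the protocol gives no effect size of its own, so power for that contrast depends on what difference is assumed.

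**What to change.** In Section 6.1 and the synopsis, name the test, the sidedness and the pairwise contrast that the calculation covers, and correct the figure. Keep 114 and state:

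> With 34 evaluable per arm, a two-sided two-sample t-test at 0.05 has about 73% power for d = 0.632 (80% for d = 0.69) for one pairwise contrast on one FMA endpoint.

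The sponsor fills in which contrast this is. Add that d = 0.632 comes from implanted VNS versus sham and was not derived for bilateral versus left, so that contrast will be reported as a difference with a 95% confidence interval. If the G\*Power run used another test or a baseline correlation, state and justify it, and replace the printed formula so that formula, inputs and result agree.

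This is a text change. It costs no patients, only a less favourable power figure. If the sponsor prefers 80% power at d = 0.632 by t-test, the matching size is 41 evaluable and 46 enrolled per arm, 138 in total, which is 138 − 114 = 24 more patients.

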### **\*\*3.2 Study Population\*\***

#### **\*\*3.2.1 Inclusion Criteria\*\***

- (1) Age between 18 and 65 years;
- (2) Diagnosed with stroke (including ischemic stroke and hemorrhagic stroke) by a qualified clinician according to the "Chinese Stroke Prevention and Treatment Guidelines" from 2021 onwards;
- (3) Stroke recovery period, stable vital signs, no disease progression;
- (4) Presence of limb motor dysfunction, diagnosed with hemiplegia.

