### **\*\*6.2 Efficacy Analysis and Statistical Methods\*\***

Statistical analysis will be performed using R software. For demographic and baseline characteristics, continuous variables conforming to normal distribution will be expressed as mean  $\pm$  standard deviation ( $\bar{x} \pm s$ ) and compared between groups using independent samples t-test; if not normally distributed, they will be expressed as median and interquartile range (IQR) and analyzed using Mann-Whitney U test. Categorical variables will be compared using Chi-square test or Fisher's exact test based on sample size and expected frequencies.

For primary and secondary outcome measures (e.g., FMA-UE, FMA-LE, WMFT, BBS, MBI scores), Linear Mixed Effects Models (LMM) will be used to handle repeated measures data, implemented via the "nlme" package in R, to assess changes over time and differences between groups, accounting for correlations within subjects across multiple time points. Post-hoc subgroup analyses will explore differential efficacy of taVNS across different stroke types (ischemic vs. hemorrhagic) and lesion locations.

For safety indicators, normality tests will first be performed on Heart Rate Variability (HRV) and blood pressure data. If normally distributed, paired sample t-tests will be used to compare values before and during treatment; if not, Wilcoxon signed-rank test will be used. Comparison of adverse event incidence rates between groups will use Chi-square test or Fisher's exact test.  $p < 0.05$  will be considered statistically significant.

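### The planning effect in 6.1 comes from implanted VNS, ischaemic stroke and the upper limb, and is carried without justification to transcutaneous stimulation, mixed stroke types and FMA-LE; 34 per arm gives about 73% power even at that effect

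*Protocol*

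**What the plan says.** Protocol 6.1 and the synopsis contain one sample size calculation. It uses a two-group formula for means with a two-sided critical value, d = 0.632 and alpha 0.05. With power "equal to 80%, the estimated sample size per group should be 34". The next step reads "Considering a 10% clinical dropout rate, the sample size per group was adjusted to 38, totaling 114 participants across three groups". No endpoint, limb or pair of arms is named.

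The effect is attributed to studies such as one cited trial, titled "Vagus nerve stimulation paired with rehabilitation for upper limb motor function after ischaemic stroke". Background section 1 (3) describes that work as finding that "implanted VNS combined with motor function training was significantly more effective than sham VNS combined with motor function training". The same sentence gives the setting of this result: "for upper limb motor function rehabilitation in ischemic stroke patients".

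This trial differs in three respects:
- **Stroke type.** Inclusion criterion (2) in 3.2.1 reads "Diagnosed with stroke (including ischemic stroke and hemorrhagic stroke").
- **Device.** Section 3.3 uses non-invasive auricular stimulation, left-sided or bilateral.
- **Limb.** Section 3.8.1 lists FMA-UE and FMA-LE as primary, without ranking them.

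Section 6.2 states: "Post-hoc subgroup analyses will explore differential efficacy of taVNS across different stroke types (ischemic vs. hemorrhagic"). It plans the same for the site of the lesion. Stroke type is recorded at baseline (3.6, item 2).

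**The concern.** A standardised effect taken from another trial supports a power statement only as far as the two trials resemble each other in intervention, population and outcome. Here all three differ, and the protocol's own background says that earlier VNS work was mainly implanted or left-sided and mainly on the upper limb. Section 6.1 gives no reason for expecting the same effect and no range of smaller effects.

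A reader of the final report will take 80% as the power of the trial for both primary endpoints. If FMA-LE or the pooled comparison is null, that reader will give the result more weight against the treatment than the planning evidence allows. Labelling the stroke-type question post hoc, although it is written down in advance, further reduces what can be learned from it.

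**Working it through.** **Inputs.** From 6.1: d = 0.632, two-sided alpha 0.05, power 80%, 34 evaluable per arm, 10% dropout, 38 enrolled per arm, 114 in total. The documents give no haemorrhagic share and no effect for haemorrhagic stroke, FMA-LE or taVNS; values for these below are assumptions.

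**1. The plan's own figure.** With d standardised (sigma = 1), the printed formula gives

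n = 2 × [(1.960 + 0.842) / 0.632]² = 2 × 4.433² = 39.3, so 40 per arm.

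The exact two-sided t-test needs 41. The stated 34 does not follow. The dropout step does reproduce: 34 / 0.9 = 37.8, so 38, and 3 × 38 = 114. Starting from 40 or 41, the same step gives 45 or 46 per arm, 135 or 138 in total.

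A one-way three-group ANOVA with f = d/2 = 0.316 does give 34 per arm. The protocol states no such test, and d/2 is the two-group conversion. In three equal arms whose largest pairwise difference is 0.632, f lies between 0.632/√6 = 0.258 (50 per arm) and 0.632 × √2/3 = 0.298 (38 per arm).

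**2. Power at 34 per arm and d = 0.632.** The noncentrality is 0.632 × √(34/2) = 2.606. The normal approximation gives Φ(2.606 − 1.960) = 74%; the exact t gives 73%. If all 38 were evaluable, the figures would be 79% and 78%. Power of 80% at 34 per arm needs d of about 0.69 (exact t).

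**3. Power at other effects** (two-sided t-test, alpha 0.05, 34 per arm; effects below 0.632 are assumed, whether because of device, limb or stroke type):

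| d | Power at 34 per arm | n per arm for 80% |
|---|---|---|
| 0.632 | 73% | 41 |
| 0.6 | 68% | 45 |
| 0.5 | 53% | 64 |
| 0.4 | 37% | 100 |
| 0.3 | 23% | 176 |

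**4. Illustration for stroke mix.** Let h be the haemorrhagic share, and assume half the effect (0.316) in those patients with equal SDs. Pooled d = (1 − h) × 0.632 + h × 0.316.

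| h | Pooled d | Power at 34 per arm |
|---|---|---|
| 20% | 0.569 | 64% |
| 30% | 0.537 | 59% |
| 40% | 0.506 | 54% |

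If the effect is equal in both stroke types, pooled d stays at 0.632 and power at 73%. Of the gap below 80% in these scenarios, about 7 points (80 − 73) come from the arithmetic in step 1 and 9 to 19 points (73 − 64 to 73 − 54) from the assumed dilution.

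**5. Can a treatment-by-stroke-type estimate separate the explanations?** Under the same assumptions the difference in effects is 0.316. For a two-arm contrast with 34 per arm, its standard error is √[2 / (34 h(1 − h))]: 0.606, 0.529 and 0.495 for h = 20%, 30% and 40%. The ratios are 0.52, 0.60 and 0.64, and two-sided power is about 8%, 9% and 10%.

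**The case against.** Borrowing an effect from a related trial is ordinary planning practice, and broad eligibility is legitimate. Both stand, and neither is criticised here. What is missing is the reason for the transfer and a range around it.

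Three stronger readings are tempting, and the documents do not support them.
- A reader might infer that the protocol claims 80% power for the lower limb. It does not say so. It gives one figure with no endpoint beside two primary endpoints. What can be said is that FMA-LE has no planning figure.
- A reader might infer that the effect is smaller in haemorrhagic stroke, on FMA-LE or with taVNS, and hence that 80% is wrong for those reasons. Nothing in the protocol shows this. Section 6.2 plans to explore a difference by stroke type, which is not the same as expecting one.
- A reader might infer that prespecifying the interaction would let the trial distinguish population mix from absence of effect. At 8 to 10% power under the assumptions in step 5, it would not.

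The primary analysis is a mixed model on repeated measures, which may be more efficient than a t-test. But 6.1 does not rely on that gain and gives no within-patient correlation from which to compute it. An SAP may add model details; the effect, its source, the power, the sample size and the post-hoc label are all fixed in the protocol.

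**Conclusion.** The point holds as a gap in justification, together with a power figure that its own inputs do not deliver. The source of d = 0.632 differs from this trial in device, stroke type and, for one of two primary endpoints, limb, and the protocol neither argues for the transfer nor discounts for it. For FMA-LE, haemorrhagic patients and taVNS, the 80% is therefore unsupported, not refuted. The loss of power from these differences cannot be derived from the documents; steps 3 and 4 only illustrate it.

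The shortfall that needs no assumption about population or device is the one at d = 0.632 itself: about 73% at 34 evaluable per arm, for a two-sided two-arm t-test at alpha 0.05. The device difference affects every stimulated patient, so it belongs in any sensitivity range at least as much as stroke type.

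**What to change.** **In 6.1 and the synopsis:**
- State that d = 0.632 is a planning assumption for FMA-UE, taken from implanted VNS in ischaemic stroke.
- Name the pair of arms that the calculation refers to.
- Restate power at 34 evaluable per arm as about 73%, so that the figure agrees with the printed formula.
- Add power at lower effects, for example 53% at d = 0.5 and 37% at d = 0.4, labelled as assumptions and covering device and limb as well as stroke type.
- State that no planning figure supports FMA-LE.

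**In 6.2 and the matching synopsis text:**
- Include baseline stroke type in the primary mixed model.
- Replace the post-hoc label for stroke type with a prespecified exploratory treatment-by-stroke-type estimate with its confidence interval.
- Note its low power (about 8 to 10% if the haemorrhagic effect is half and the share is 20 to 40%), so that it is not read as explaining a null result.

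**Cost.** Wording in two sections and the synopsis, and a less favourable stated power. No new data are needed, since stroke type is already collected, and enrolment stays at 114.
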